**Methods:**

In this mixed-methods study, our primary objective is to assess, for babies born at 27–31 weeks gestation and admitted to a neonatal unit in England, whether care in an NICU vs an LNU impacts on survival and key morbidities (up to age 1 year), at each gestational age in weeks. Routinely recorded data extracted from real-time, point-of-care patient management systems held in the National Neonatal Research Database, Hospital Episode Statistics and Office for National Statistics, for January 2014 to December 2018, will be analysed. Secondary objectives are to assess (1) whether differences in care provided, rather than a focus on LNU/NICU designation, drives gestation-specific outcomes, (2) where care is most cost-effective and (3) what parents’ and clinicians' perspectives are on place of care, and how these could guide clinical decision-making. Our findings will be used to develop recommendations, in collaboration with national bodies, to inform clinical practice, commissioning and policy-making. The project is supported by a parent advisory panel and a study steering committee.

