#### Population

All babies born at 27–31 weeks gestation between 1 January 2014 and 31 December 2018, in an English hospital with an LNU or NICU, whose records are captured within the National Neonatal Research Database (NNRD) will be included. With approximately 6000 babies per year in England meeting our criteria, the study is expected to include data on approximately 30 000 babies. Data on births and transfers to and from an SCBU will also be captured, to provide baseline information of place of birth, care and transfer across all neonatal units in England for this gestational age range.

Data sources:

Neonatal data: The NNRD will provide data on admissions to LNU or NICU in England. The NNRD is maintained by the NDAU and created from electronic health records.^21^ It includes the information on characteristics of mothers and babies (eg, maternal pregnancy information, baby’s birth weight, sex and gestational age), admission-related episodes (eg, reason for admission, admission temperature, length of stay and the number of episodes of care) and daily neonatal care of the babies after birth (eg, treatment, clinical procedures and morbidities).Postneonatal data: To assess outcomes (survival and morbidities) to 365 days of age, the NNRD data will be linked to:Hospital Episode Statistics (HES): information all admissions, outpatient appointments and accident and emergency attendances at NHS hospitals in England.Office for National Statistics (ONS): information on location, date and cause of death, obtained from death registration records.

Neonatal units will be allowed to assess the quality of their data entry onto electronic records, based on completion of data being fed back to neonatal units for surfactant replacement, nitric oxide and discharge home on oxygen.

Inclusion and exclusion criteria: Units will be offered an opt-out option at the start of the project. The confidentiality of neonatal units who chose to opt out will be respected. A minimum dataset describing these units will only be reported if it is possible to maintain their anonymity in this process.

Clinical outcomes: The primary outcome for workstream 1 is death before discharge from a neonatal unit. We expect a within-unit mortality percentage of approximately 5% in this group. Information on deaths outside of neonatal care will be provided from ONS.

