XA03Z	Neonatal critical care, special care, carer not resident alongside baby	£605
XA04Z	Neonatal critical care, special care, carer resident at cot side and caring for baby	£435
XA05Z	Neonatal critical care, normal care	£441
XA06Z	Neonatal critical care, transportation	£1159

HRG, Healthcare Resource Group; NHS, National Health Service.

The costs of standard care provided by NICU or LNU, unit costs will be multiplied by the number of days using different levels of care. Since the standard packages costed by HRG codes do not include all major clinical activities, we will also cost the use of selected relevant procedures. These will include nitric oxide, surfactant replacement, total parental nutrition, ultrasound scanning, blood transfusion and palivizumab therapy. Cost data for these activities will be obtained from literature reviews and extracted from selected hospital finance departments as needed. The cost of surgical procedures are included in the standard care package by the level of care defined by HRG codes and will not be costed separately. Key components of healthcare resource use will be presented separately from associated costs as currently recommended.

Original neonatal care information will be linked to HES to extend the time horizon of the economic evaluation to 1 year of corrected age. A comprehensive cost analysis using the methodology above will be conducted to identify whether patterns of service use of hospital admissions, outpatient visits and accident and emergency services differs across neonatal strategies at 1-year-follow-up.

The number of lives saved will be the health outcome measure that will be used in the economic evaluation. Deaths occurring after discharge from the neonatal unit will be informed by the ONS linked. An incremental analysis of costs and health outcomes between NICUs and LNUs will be conducted and synthesised using the net-benefit framework. Current thresholds of willingness to pay as recommended by the National Institute for Health and Care Excellence (NICE) will be used to determine value for money.

We will follow current guidance for methods of technology appraisal to present and report the results of the economic analysis.^31–33^

### Workstream 2

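### The economic evaluation runs to 1 year of corrected age, but the linkage for survival and morbidities stops at 365 days of age

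*Protocol article*

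**What the plan says.** The protocol article states the length of follow-up in several places.

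- **Workstreams 1 and 3, analysis of healthcare costs and cost-effectiveness.** Neonatal records are to be "linked to HES to extend the time horizon of the economic evaluation to 1 year of corrected age". The same paragraph then asks whether service use "differs across neonatal strategies at 1-year-follow-up", without saying whether that year is chronological or corrected.
- **Same section, health outcome.** "The number of lives saved will be the health outcome measure that will be used in the economic evaluation". For later deaths: "Deaths occurring after discharge from the neonatal unit will be informed by the ONS linked". Neither sentence gives an age limit.
- **Population, data sources, postneonatal data (same joint heading).** "To assess outcomes (survival and morbidities) to 365 days of age, the NNRD data will be linked to" HES and ONS.
- **Abstract, Methods.** The primary objective is whether place of care "impacts on survival and key morbidities (up to age 1 year), at each gestational age in weeks". The year is not described as corrected.

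Two further statements bear on calendar time. The abstract closes its list of sources with "Hospital Episode Statistics and Office for National Statistics, for January 2014 to December 2018, will be analysed". The Population paragraph uses the same dates to define the cohort: "All babies born at 27–31 weeks gestation between 1 January 2014 and 31 December 2018".

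**The concern.** One year of corrected age and 365 days of age are different endpoints for every baby in this cohort, and they are furthest apart for the least mature. Lives saved has no horizon of its own. It draws on the ONS linkage, and the only age limit stated for that linkage is 365 days. Read that way, a baby who dies after day 365 but before 1 year of corrected age counts as a survivor, while hospital costs are still being collected over that interval.

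The incremental analysis sets costs against lives saved in a net-benefit framework, so both should cover the same stretch of life. The mismatch also varies with gestational age, and the study wants week-by-week conclusions. The Background says that if key clinical outcomes do not differ between unit types, cost-effectiveness and family satisfaction should drive how services are delivered. The economic result may therefore carry weight in the recommendations.

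The calendar dates raise a separate, lesser question. The abstract attaches to HES and ONS the same closing month as the last birth, and no later end date for the linked data is given.

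**Working it through.** **Inputs.** Gestation 27+0 to 31+6 weeks (Background). Births from 1 January 2014 to 31 December 2018, which is 1,826 days, and about 6,000 babies a year (Population). Horizons of 365 days and of 1 year corrected age (as quoted above). Assumptions: term is 40+0 weeks (280 days), and births are spread evenly over time.

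**The plan's own figure.** 6,000 × 5 = 30,000 babies, which agrees with the stated cohort size.

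**Step 1: the horizon gap.** Day of life at 1 year corrected age = 365 + (280 − gestational age in days).

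- Born at 27+0 (189 days): 280 − 189 = 91, so day 365 + 91 = 456.
- Born at 31+6 (223 days): 280 − 223 = 57, so day 365 + 57 = 422.

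The cost window is longer than the survival window by 57/365 = 16% to 91/365 = 25% in days. By completed week the excess is:

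| Week of birth | Excess over 365 days |
|---|---|
| 27 | 85 to 91 days |
| 28 | 78 to 84 days |
| 29 | 71 to 77 days |
| 30 | 64 to 70 days |
| 31 | 57 to 63 days |

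Within a week the gap varies by at most 6 days. Across the range it varies by 91 − 57 = 34 days.

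**Step 2: end dates needed to follow the last birth fully.**

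- 31 December 2018 + 365 days = 31 December 2019.
- 31 December 2018 + 422 days = 26 February 2020.
- 31 December 2018 + 456 days = 31 March 2020.

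**Step 3: only if the linked data really end on 31 December 2018.** The share of babies with incomplete follow-up is the horizon divided by 1,826.

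- 365 days: 365/1,826 = 20.0%, about 6,000 of 30,000. The last fully followed birth is 31 December 2017.
- Corrected age, born at 31+6: 422/1,826 = 23.1%, about 6,930. The last fully followed birth is 4 November 2017.
- Corrected age, born at 27+0: 456/1,826 = 25.0%, about 7,490. The last fully followed birth is 1 October 2017.

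If the dates describe births only and linkage continues for each baby, these shares are zero and only the gap in step 1 remains.

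**The case against.** The economic text extends the horizon of the whole evaluation, not of costs alone. It names lives saved as that evaluation's outcome and puts no 365-day cap on the ONS deaths. Taken by itself, it can be read as one horizon for both. This stands as a possible reading, but it does not remove the conflict: the 365-day limit sits under the heading shared by workstreams 1 and 3 and is the only limit given for that linkage. Two rules are stated and they differ.

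A reader might infer that the one-year economic results cannot be interpreted. The documents do not support that. Within a gestational week the gap is nearly the same for NICU and LNU babies, so by itself it favours neither. A window 16% to 25% longer in days is not a change of that size in cost or in deaths.

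A reader might also infer that a fifth to a quarter of the cohort will lack one-year follow-up. That rests on one sentence of the abstract. The same paragraph promises outcomes to age 1 year, and the Population section uses those dates as birth dates and plans linkage to 365 days. The more natural reading is that the abstract names the birth cohort loosely. A condensed article may also leave the exact extraction date to the full protocol.

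Finally, a reader might infer that babies still in hospital at the end of 2018 would compromise the primary outcome, death before discharge. Nothing says that neonatal records are cut off on that date, and no length of stay is given from which to count such babies.

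**Conclusion.** The article gives two conflicting horizons for the one-year work, and the two statements must be reconciled. Followed as written, costs run past survival follow-up by 57 days (born at 31+6) to 91 days (born at 27+0), with term at 40+0 weeks, so incremental costs and lives saved do not share a horizon. The effect on incremental cost, lives saved or net benefit cannot be calculated from the documents. Costs to hospital discharge and the primary mortality outcome are untouched.

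The 20% and 23% to 25% figures are conditional on linked data that truly close on 31 December 2018, which is not established. On the calendar dates, the article needs only a clarification.

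**What to change.** Use one horizon for costs, deaths and post-discharge morbidity, and state it identically in the data sources text and in the economic methods, including the sentence on service use at one year. Choosing 365 days of age needs the fewest changes, since the data sources text already says so and the abstract's limit of age 1 year fits it. Corrected age is equally consistent if it is applied to all three.

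State in the abstract that January 2014 to December 2018 is the birth window, and that HES and ONS follow-up runs to at least 31 December 2019 (31 March 2020 if corrected age is used).

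If the linked data do end on 31 December 2018, restrict the one-year analyses to births with complete follow-up. That means births before 1 January 2018 for 365 days. For corrected age it means births no later than 1 October 2017 (born at 27+0) to 4 November 2017 (born at 31+6), depending on gestation.

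The cost is a few sentences. A later end date on the linkage request is needed only if the request does not already cover it, and the article does not show this.

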## Dissemination

Written information materials have been developed for both parents and clinicians invited to participate in the ethnographic study.Presentation and publication: This will include presentation of research findings at national and international conferences, and publication in peer-reviewed journals.Development of recommendations for care of the neonate born at 27–31 weeks gestation: A working group will be formed with BAPM and BLISS, to develop position statements and recommendations regarding the most appropriate place of care for babies born at this gestation in England. This will be led by investigators from the study and will incorporate nursing and medical professionals with relevant expertise, and representatives from the project’s parent advisory panel.Consultation with healthcare professionals and other stakeholders: Framework documents and recommendations will be processed through BAPM. This includes consultation with members and stakeholders (managerial stakeholders including Commissioners, Networks, Trusts, Governmental/Regulatory stakeholders including the Department of Health, Public Health England, National Commissioning Board, Care Quality Commission, NICE and educational stakeholders including Royal Colleges and professional societies).Publication and dissemination of recommendations: Recommendations will be published via BAPM and RCPCH. Further dissemination will occur via the neonatal CRG to inform evidence-based commissioning of neonatal services, and BLISS to inform written information for parents, parent counselling and support services.
